#### Participant timeline {13}

Table 3 describes the stages of the whole study period. Figure 1 illustrates the participant flow from screening to reference testing.

**Table 3 Tab3:** STUDY PERIOD

	Enrolment	***Allocation***	Observational period			Close-out
**TIMEPOINT**	-t_1_	Not applicable	t_1_ (CT-imaging/inspection of cineradiography reports)	t_2_ (arthroscopy/inspection of surgical reports)	t_3_ (discharge)	t_x_ (statistical analysis index test vs. reference test, see flow chart)
**ENROLMENT:**						
Eligibility screening (patients/files)	X					
Informed consent	X					
**STUDY GROUPS:**						
4D CT (prospective)			x	x	x	x
Cineradiography (retrospective)			x	x	x	x
**ASSESSMENTS:**						
Stability			x	x		
Effective skin dose 4D CT			x

**Fig. 1 Fig1:**
[figure not shown]
Flow diagram to test diagnostic accuracy of 4D CT and cineradiography in comparison

#### Sample size {14}

The study will be conducted and analyzed in an exploratory fashion. Therefore, formal sample size calculations are deferred by the investigators. Instead, yearly patient numbers were estimated, and the number of participants was adapted to a two-year study design which results in a recruiting target of 40 patients used for estimation of diagnostic accuracy of 4D CT. The comparative historical cohort used for estimation of diagnostic accuracy of cineradiography should consist of 80 patients to account for a probably greater extent of heterogeneity in the retrospective data due to the fact that these were collected by different clinicians who were not instructed on data collection specifically for this trial.

#### Recruitment {15}

Previously, approximately 30 arthroscopies have been performed at the study center for suspected SLL tears each year. Thus, enrolment of 40 patients in 2 years seems reasonable. To assure maximum screening and identification of eligible patients, all hand surgeons at the center will be involved in the process. Radiologists are sensitized to communicate radiographs with abnormalities of the SL joint to increase the screening cohort.

### Assignment of interventions: allocation

#### Sequence generation {16a}

The prospective part of the trial is a single arm observational study of diagnostic accuracy of 4D CT.

A historical cohort serves as a comparative group diagnosed through cineradiography preoperatively. The switch of the diagnostic/imaging standard at the study center from cineradiography to 4D CT for diagnosing instable SLL tears results in allocation to the historical and prospective group. Randomization is not part of this trial.

#### Concealment mechanism {16b}

Not applicable.

#### Implementation {16c}

Patients will be enrolled prospectively by attending hand surgeons and radiologists.

### Assignment of interventions: blinding

#### Who will be blinded {17a}

Hand surgeons will be blinded to the results of 4D CT and radiologists will be blinded to the results of arthroscopies. Both departments will supply the statistician with their results.

Radiologists were unaware of the results of arthroscopy while reporting cineradiograms prior to surgery but hand surgeons were aware about imaging results preoperatively.

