### Objectives {7}

Primary objectives:
Analysis of diagnostic accuracy of 4D CT for the differentiation between stable and instable SLL tears preoperatively.Comparison of diagnostic accuracies of 4D CT and cineradiography.

*Secondary objectives:*
Can 4D CT scans of the wrist detect secondary injuries as opposed to radiography?How do the stages of scapholunate dissociation correlate with the time interval between diagnostics and trauma?Are measured effective radiation skin doses in-vivo and calculated skin doses during 4D CT similar?Which diagnostic algorithm can be proposed for suspected SLL tears?

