### Trial design {8}

Prospective, exploratory study of diagnostic accuracy of 4D CT with arthroscopy as reference test adhering to the Standards for Reporting of Diagnostic Accuracy Studies (STARD) guidelines [15].

Additional comparison of sensitivity and specificity of 4D CT in detecting instable SLL tears to that of cineradiography observed in a historical cohort.

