#### Intervention description {11a}

All patients with a typical trauma mechanism and wrist pain presenting through the ambulance or emergency room will be screened for eligibility. Patients will be examined and will receive radiographs of the wrist in two planes routinely. In cases of suspected SLL tear and indication for arthroscopy, patients will be informed about the possibility of study participation by the attending hand surgeon.

According to the inclusion and exclusion criteria 40 participants will be enrolled consecutively after written consent.

4D CT scans of the injured wrist will be performed preoperatively and analyzed by two specialized radiologists. Coronal reconstructions will be used to measure the maximum and minimum scapholunate distance (SLD). On sagittal reconstructions the scapholunate (SL) and radiolunate (RL) angle will be determined to classify SLL tears as stable or unstable.

The patients will not be exposed to radiation for research purposes. Arthroscopy will be performed as the diagnostic gold standard within the same week to classify the type of SLL tear according to the European Wrist Arthroscopy Society (EWAS) and Geissler [16, 17]. Primary reconstruction and temporary arthrodesis will be performed when necessary, but the surgical therapy will not be part of the study.

We will conduct an additional screening of historical patient records for eligibility, inclusion, and exclusion criteria. These historical patients with a typical trauma and wrist pain were also examined clinically and received radiographs of the wrist in two planes routinely. In cases of suspected SLL tear, cineradiography was performed before arthroscopy. After written consent 80 consecutive patient who were diagnosed through cineradiography before arthroscopy will be enrolled. Measurement of minimum and maximum SLD on anterior-posterior projections, of SL angle, and RL angle on lateral projections will be measured to classify SLL tears as stable or unstable and to compare these results to the findings of arthroscopy. The diagnostic accuracy of cineradiography will serve as a comparison for the sensitivity and specificity of 4D CT in suspected SLL tears.

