## Discussion

Studies of diagnostic accuracy have the potential to improve the standard of medical care. Well conducted studies which are reported adhering to standardized guidelines allow for a generalizability of the topic [15]. Observational studies have the advantage of answering certain scientific questions in a rather descriptive manner while excluding any harm induced by study specific interventions. The lack of direct comparisons through a strict randomization protocol is a disadvantage of this study type.

On these grounds it can be expected that this prospective observational study will result in reliable calculations of diagnostic parameters of 4D CT of the wrist in diagnosing instable SLL tears. The comparison with a historical cohort on the other hand, will always be a means to atone for missing randomization and prospective comparisons.

In order not to over-estimate the clinical relevance of 4D CT, it will be crucial to minimize drop-outs after conducting the index test. The study protocol requires that all patients will have to have an indication for the reference test arthroscopy first to be eligible as participants. The number and reasons for drop-outs and excluded patients will be described in detail in the study report.

It can be expected that a positive outcome of the study and an increasing availability of 4D CT could have a grave impact on out-patient care. Since approximately 5% of all wrist sprains have an associated injury of the SLL [27], a broad availability of reliable primary imaging might improve early detection rates, reduce the incidence of resulting osteoarthritis, and the number of unnecessary diagnostic arthroscopies in the future.

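### The 4D CT versus cineradiography contrast, listed as primary, sets a blinded arthroscopy reference against an unblinded one, and the historical route to arthroscopy is not shown to match

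*Protocol article*

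**What the plan says.** **Status of the comparison.** Objectives {7} has two primary objectives, the second being "Comparison of diagnostic accuracies of 4D CT and cineradiography". Trial design {8} describes the same analysis as "Additional comparison of sensitivity and specificity of 4D CT in detecting instable SLL tears to that of cineradiography observed in a historical cohort".

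**Blinding of the reference.** Under Who will be blinded {17a}, the prospective rule is "Hand surgeons will be blinded to the results of 4D CT". For the historical cohort the same section reports "Radiologists were unaware of the results of arthroscopy while reporting cineradiograms prior to surgery", but also that "hand surgeons were aware about imaging results preoperatively".

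**Route to arthroscopy.** Intervention description {11a} brings prospective patients into the study once a tear is suspected and arthroscopy is already indicated; 4D CT follows. For historical patients it says "In cases of suspected SLL tear, cineradiography was performed before arthroscopy", and it enrols only those who had both examinations. It does not say whether arthroscopy had been indicated before the cineradiogram.

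**Analysis.** Statistical methods {20a} plans AUC, sensitivity and specificity with 95% confidence intervals for each index test, all exploratory. Sample size {14} sets 40 prospective and 80 historical patients, the larger number being meant to allow for heterogeneity in retrospective data. The Discussion concedes the absence of randomisation and of a prospective comparator. It names neither the unblinded historical reference nor the indication path.

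**The concern.** A comparison of two index tests in separate cohorts is fair only if the reference standard was obtained in the same way in both. Here one difference is documented and a second is possible.

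The documented difference is blinding. Arthroscopic staging rests partly on the surgeon's judgement of how far the joint widens under the hook (Table 2). A surgeon who knows the cineradiogram may lean towards it, which raises the apparent sensitivity and specificity of cineradiography. 4D CT gets no such help.

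The possible difference is verification. If a normal cineradiogram made arthroscopy less likely, image-negative patients are under-represented among the 80. Apparent sensitivity then rises and apparent specificity falls.

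A between-test difference could therefore reflect how the reference was obtained rather than the modality. A confidence interval does not show this, and 80 rather than 40 historical patients narrows the interval without removing the bias.

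**Working it through.** The protocol gives no accuracy, prevalence, effect size or power, so there is no figure of its own to reproduce. Everything below except the cohort sizes (40 and 80, Sample size {14}) is assumed.

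**Assumed inputs.** True cineradiography sensitivity (Se) 0.75 and specificity (Sp) 0.85. Half of wrists unstable, giving 20 versus 40 unstable and 20 versus 40 stable. k is the arthroscopy rate in image-negative patients divided by that in image-positive patients. r is the share of arthroscopic calls that simply follow the image.

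**1. Partial verification alone.**
Apparent Se = Se / (Se + (1 − Se)·k). Apparent Sp = Sp·k / (Sp·k + (1 − Sp)).

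| k | Apparent Se | Apparent Sp |
|---|---|---|
| 1.0 | 0.75/1.000 = 75% | 0.85/1.000 = 85% |
| 0.7 | 0.75/0.925 = 81% | 0.595/0.745 = 80% |
| 0.5 | 0.75/0.875 = 86% | 0.425/0.575 = 74% |
| 0.3 | 0.75/0.825 = 91% | 0.255/0.405 = 63% |

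At k = 1 there is no distortion.

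**2. Unblinded reference alone.** Per 100 wrists: 37.5 true positives, 12.5 false negatives, 7.5 false positives, 42.5 true negatives. A share r of each discordant cell moves to agree with the image.
- r = 10%: false negatives 11.25, true negatives 43.75, false positives 6.75, true positives 38.25. Se = 38.25/49.50 = 77%; Sp = 43.75/50.50 = 87%.
- r = 25%: 9.375, 45.625, 5.625 and 39.375 in the same order. Se = 39.375/48.75 = 81%; Sp = 45.625/51.25 = 89%.
- r = 0: no distortion.

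**3. Both, k = 0.5 and r = 10%.** The image-negative cells in step 2 are halved: false negatives 5.625, true negatives 21.875. Se = 38.25/43.875 = 87%; Sp = 21.875/28.625 = 76%. The two mechanisms add up for sensitivity and partly cancel for specificity.

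**4. Scale against precision.** The half-width for a sensitivity difference is 1.96·√(p₁(1 − p₁)/20 + p₂(1 − p₂)/40).
- 0.80 in both: 1.96·√(0.008 + 0.004) = 21 points.
- 0.75 in both: 1.96·√(0.009375 + 0.0046875) = 23 points.
- 0.90 versus 0.75: 1.96·√(0.0045 + 0.0046875) = 19 points.

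For specificity at 0.85 in both: 1.96·√(0.006375 + 0.0031875) = 19 points.

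The modelled sensitivity shifts from a single mechanism run from 0 to 16 points, inside the half-width. The specificity shift reaches 22 points only at k = 0.3.

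**5. What a correction can do.** At k = 0.5 with no review bias, Begg-Greenes divides the image-negative cells by 0.5 and returns 75/85. In the combined case of step 3, the same division gives 38.25/(38.25 + 11.25) = 77% and 43.75/(43.75 + 6.75) = 87%. It removes the verification effect and leaves the effect of the unblinded reference untouched.

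**The case against.** **Selection on the image is not documented.** A reader might infer from the historical pathway that partial verification took place. No passage says that cineradiography decided who had arthroscopy. The Background says arthroscopy was long the norm for any suspected tear because imaging was not trusted, which would keep k near 1. Eligibility {10} applies the same criteria to both cohorts, and the Discussion says "all patients will have to have an indication for the reference test arthroscopy first to be eligible as participants". The last two carry limited weight: the criteria list contains no arthroscopy indication, and the Discussion sentence stands in a paragraph on drop-outs after the index test. The objection holds this far: selection is an open question, probably smaller than the low values of k suggest, and not a fact.

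**Review bias may be weak.** Eligibility {10} has two radiologists evaluate the cineradiographies independently, while Table 3 refers to inspecting the reports. If the images are re-read, the analysed reading is not the one the surgeon knew. Table 2 also relies on physical tests with hook and arthroscope. Both points limit the bias without removing it, because two readings of the same image will tend to agree.

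**The study is exploratory.** No test and no superiority or equivalence claim is planned, and the protocol openly discloses that the historical surgeons were unblinded. That excuses low power. It does not excuse a systematic difference in the reference standard behind an objective labelled primary.

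**Begg-Greenes fits imperfectly.** It assumes that verification depends only on the recorded image result, although clinical examination and radiographs also feed the indication. It also needs an archive that the protocol does not describe. This stands, and the fix is conditional for that reason.

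**Conclusion.** The concern holds in limited form and should be fixed. Two points are plain from the text: the comparison is primary in one section and supplementary in another, and its reference standard is blinded to the index test in only one cohort. A third is a gap: the arthroscopy indication is not stated to precede cineradiography.

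The contrast is therefore at serious risk of bias whose size the protocol does not allow one to derive. On the assumed 75/85, the scenarios run from no shift to 16 points in sensitivity and 22 points in specificity, against half-widths of roughly 20 points. The direction for specificity depends on which mechanism dominates.

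Two stronger readings are not supported. One is that the bias equals any difference the study could detect. With 20 versus 40 unstable wrists, Fisher's test would need about 90% versus 55%, a 35-point gap, for 80% power, and no such test is planned; the largest single-mechanism sensitivity shift is 16 points. The other is that the trial's results as a whole cannot be interpreted. The first primary objective, 4D CT against arthroscopy by surgeons blinded to it, is unaffected.

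**What to change.** 1. Reconcile Objectives {7} with Trial design {8} by making the 4D CT versus cineradiography comparison secondary and descriptive.
2. State in Intervention description {11a} whether arthroscopy was indicated before cineradiography in the historical cohort.
3. As far as archive records allow, count all cineradiographies for suspected SLL tear in the same years, by result and by whether arthroscopy followed.
4. If the arthroscopy rate differs by result, report Begg-Greenes corrected sensitivity and specificity beside the raw values. State its assumption, and use the same image reading as the main analysis.
5. Add a simple sensitivity range for the unblinded reference, for example r = 0, 10% and 25% as in step 2 of the working, since the verification correction does not address it.
6. Name both mechanisms and their directions in Statistical methods {20a}, and draw no superiority or equivalence conclusion from the raw contrast.

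The cost is a record count, a little extra analysis and the loss of the primary label. No change to recruitment, imaging or patient care is involved.

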#### Procedure for unblinding if needed {17b}

Unblinding of attending physicians is not permissible. Patients will receive the therapeutic standard which is guaranteed by arthroscopy independent of the results of 4D CT.

### Data collection and management

#### Plans for assessment and collection of outcomes {18a}

Hand surgeons will be trained to examine patients during screening in a standardized fashion. Arthroscopies will be performed with the patient under general or regional anesthesia. At first, the membranous or proximal part of the SLL complex is visualized and the tear located through a 3/4 and 5 U portal. The SLL will be examined using a 2.4-mm arthroscope with a 30° wide angle lens (Storz, Erlangen, Germany) and probed with a hook. A tear will be differentiated into an avulsion from the lunate or scaphoid or a midsubstance ligament rupture. Secondly, through the midcarpal ulnar (MCU) and midcarpal radial (MCR) portals the SLL tear will be classified. Surgical reports will be descriptive, but they will include a final EWAS/Geissler classification to describe stability of the SL joint on a case report form (CRF) [16, 17]. The following data will be documented by hand surgeons on paper CRFs [Table 4].

**Table 4 Tab4:** Case Report Form

Patient-ID:		
**Screening:** Date		
Suspected SLL tear	Yes	No
Indication for arthroscopy	Yes	No
> 18 Years	Yes	No
Ability to perform radio-ulnar motion	Yes	No
Written informed consent	Yes	No
**Exclusion criteria:** Date		
Pregnancy	Yes	No
Incompliance for radio-ulnar motion		
SLAC	Yes	No
**Enrolment:** Date		
Date of enrolment		
**Epidemiology:**		
Gender	Male	Female
Side of injury	Right	Left
Handedness	Right	Left
Date of injury		
Age at the day of injury		
**Clinical examination:** Date		
Watson-Test	Positive	Negative
Localized pain during compression of dorsal SLL	Yes	No
**Arthroscopy:** Date		
Age at the day of arthroscopy		
EWAS/Geissler Stadium		
Stability	Stable	Unstable

4D CTs will be acquired using a dual-source scanner with 2 × 192 rows and a detector width of 6 cm (Somatom Force, Siemens, Germany). Patients will be placed in prone position with the injured wrist reaching into the gantry (“superman position”). Patients will be instructed to perform a radio-ulnar movement during an 8 s scan cycle. Forearms will only be lightly fixated with a tape as a reminder for the patients to reside to wrist movements only. Postprocessing will be performed using a designated software (Syngo.Via Version VB10B-VB30A, Siemens, Germany). Reconstructions include dynamic 5 mm and 1 mm coronal reconstructions as well as static coronal and sagittal reconstructions of 2 mm. Table 5 summarizes the acquisition parameters of 4D CT.

**Table 5 Tab5:** Parameters of 4D CT

Tube voltage (kV)	80
Milliamperage (mAs)	70
Section thickness (mm)	1
Length (mm)	56
Number of slices	1254
Collimation	384 × 1 mm
Reconstruction matrix	Soft-tissue and bone kernel
Image reconstruction	512 × 512

Radiologists will document results of 4D CT in a standardized manner to describe stability of the SLL ([20], Table 6). SLD will be measured in the center of the SL joint during radio-ulnar motion at minimum and maximum width [21, 22]. Carpal angles will be measured on sagittal reconstructions according to the radial axis [23, 24].

**Table 6 Tab6:** Radiological Report

Patient-ID:		
**Parameter:** Date		
Modality	4D CT	Cineradiography
Date of imaging		
SLD_min_		
SLD_max_		
SL angle		
RL angle		
**Stability**	Stable	Unstable
**Effective skin dose of 4D CT**		
1 ipsilateral hand		
2 ipsilateral shoulder		
3 head		
CT dose index		
Dose length product		

### Plans to promote participant retention and complete follow-up {18b}

This observational study will report on diagnostic accuracies of 4D CT and cineradiography. The observation will end with discharge. Follow-up examinations will not be part of this study. Plans to promote participant retention are not required.

### Data management {19}

Data will be collected on paper CRFs and stored in the study center in each department for the duration of the study and 5 years thereafter. Paper CRFs will be copied into digital files in excel format and protected by departmental passwords. Data will be checked for completeness during digitalization. Only one of the attending physicians of each department is selected for data management and digitalization. Digitally secured data will be transferred on hard drives to the statistician at the end of data collection.

### Confidentialitesy {27}

Patient information will be collected and processes only by attending physicians. For study purposes, patient information will be pseudonymized during analysis by each department independently. The lists for decoding pseudonyms will be kept in a password secured and firewall protected PC at each department. The statistician will possess a master key to match pseudonyms of each department to recombine the participants results for analysis. Radiologists and hand surgeons will collect data separately on paper CRFs. Data will be entered into digital tables secured with departmental passwords and checked for completeness. The statistician will receive data from both departments separately for analysis. Study data won’t leave the study center. Publication of anonymous data independently of the study results is planned.

### Plans for collection, laboratory evaluation and storage of biological specimens for genetic or molecular analysis in this trial/future use {33}

Not applicable.

### Statistical methods

#### Statistical methods for primary and secondary outcomes {20a}

All statistical analyses will be conducted in an exploratory, hypotheses-generating fashion. For both index tests AUCs as well as sensitivity and specificity with 95% confidence intervals will be calculated. Descriptive statistics dependent on scale and distribution will be reported for all parameters.

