#### Methods for additional analyses (e.g. subgroup analyses) {20b}

Interobserver agreement for cineradiographies and 4D CT between two radiologists will be evaluated using the kappa statistic.

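### The 4D CT versus cineradiography comparison is listed as a primary objective, but the stated analysis never estimates the difference between the two cohorts

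*Protocol article*

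**What the plan says.** Objectives {7} gives two primary objectives. The second is "Comparison of diagnostic accuracies of 4D CT and cineradiography". Trial design {8} describes the same item as "Additional comparison of sensitivity and specificity of 4D CT in detecting instable SLL tears to that of cineradiography observed in a historical cohort".

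The section on statistical methods for primary and secondary outcomes {20a} states: "For both index tests AUCs as well as sensitivity and specificity with 95% confidence intervals will be calculated". It adds descriptive statistics and says "All statistical analyses will be conducted in an exploratory, hypotheses-generating fashion". Section {20b} adds one analysis: "Interobserver agreement for cineradiographies and 4D CT between two radiologists will be evaluated using the kappa statistic". None of these names a difference, a ratio, a between-cohort interval, or a stratified or adjusted contrast.

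Sample size {14} sets 40 prospective patients from patient flow, without a formal calculation, and 80 historical patients because greater heterogeneity is expected in the retrospective data. Section {20c} repeats that reason. Allocation to cohort follows the change of imaging standard at the centre ({16a}). Eligibility criteria are the same in both cohorts ({10}). Under {17a}, surgeons are blinded to 4D CT, whereas in the historical cohort they knew the imaging result before arthroscopy.

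**The concern.** An exploratory label removes the need for a hypothesis test. It does not remove the need to estimate the quantity that an objective names. For a comparison that quantity is a between-cohort difference, and the methods section supplies only its two ingredients. A reader of the final report would set one interval against the other, and that is a poor guide to the size and uncertainty of the difference.

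Two further matters affect how the crude contrast can be read. First, sensitivity for instable tears may depend on how advanced the tears are, and the stage mix could differ between cohorts from different periods. Recruitment {15} describes one possible source on the prospective side: "Radiologists are sensitized to communicate radiographs with abnormalities of the SL joint to increase the screening cohort". Second, the reference standard was read with knowledge of the index test in one cohort only. The plan's sole answer to heterogeneity is more historical patients. That reduces random error and leaves bias untouched.

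The rank of the comparison is also inconsistent between {7} and {8}, so a reader cannot tell how much weight it is meant to carry.

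**Working it through.** **The plan's own figure.** The protocol gives no power or precision calculation to reproduce. The target of 40 is a feasibility number: about 30 arthroscopies a year × 2 years = 60, and 40/60 = 67%. That is consistent with Recruitment {15}.

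**Inputs that the documents do not give.** The share of instable tears, the accuracies and the stage mixes below are assumptions. With 30%, 50% or 70% instable, 40 and 80 patients yield 12 v 24, 20 v 40 or 28 v 56 instable wrists.

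**Step 1: separate intervals against a difference interval.** Take 19/20 = 95% for 4D CT and 28/40 = 70% for cineradiography.
- Wilson 95% intervals: 76.4% to 99.1%, and 54.6% to 81.9%. They overlap between 76.4% and 81.9%.
- Newcombe interval for the difference d = p1 − p2 = 0.25, with l and u the Wilson limits:
  - lower = d − √[(p1 − l1)² + (u2 − p2)²] = 0.25 − √[0.1861² + 0.1193²] = 0.25 − 0.221 = +0.029
  - upper = d + √[(u1 − p1)² + (p2 − l2)²] = 0.25 + √[0.0411² + 0.1543²] = 0.25 + 0.160 = +0.410
- The interval for the difference, +2.9 to +41.0 points, excludes zero although the separate intervals overlap.

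**Step 2: how often this matters.** Exact binomial enumeration, true sensitivities 0.90 v 0.70:

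| Instable wrists | Wilson intervals do not overlap | Newcombe difference interval excludes 0 |
|---|---|---|
| 12 v 24 | 0.04 | 0.23 |
| 20 v 40 | 0.13 | 0.40 |
| 28 v 56 | 0.25 | 0.55 |

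At 0.95 v 0.75 with 20 v 40 wrists the figures are 0.124 and 0.470. With equal sensitivities of 0.80 and 20 v 40 wrists they are 0.004 and 0.045. These figures describe what an informal comparison of intervals would do. They do not describe a rule in the protocol.

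**Step 3: precision even with the right estimate.** 18/20 v 32/40 is a difference of +10 points, Newcombe interval −12.2 to +26.4. For 80% power at 0.90 v 0.70 about 49 v 98 instable wrists would be needed, more than the 40 and 80 patients in total.

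**Step 4: what stage mix could do.** Suppose both tests have the same stage-specific sensitivity, and stages IV–V make up 60% of instable tears in one cohort and 30% in the other.
- With 0.98 (IV–V) and 0.70 (III): 0.98×0.6 + 0.70×0.4 = 0.868; 0.98×0.3 + 0.70×0.7 = 0.784; gap 8.4 points.
- With 0.95 and 0.60: 0.95×0.6 + 0.60×0.4 = 0.810; 0.95×0.3 + 0.60×0.7 = 0.705; gap 10.5 points.
- Other assumed mixes gave gaps of 5 to 7.5 points.

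The gap is produced by mix alone, and its sign depends on which cohort has the more advanced tears. The documents do not show that. The Background {6a} says radiographs are accurate only for static injuries, and Table 2 ties stage V to pathological plain radiographs. It is therefore plausible that flagging abnormal radiographs shifts the mix, but no more than plausible.

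**The case against.** The strongest reply has four parts.

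- **No overlap rule is written.** A reader might infer that the comparison will be decided by whether the two intervals overlap. The protocol states no test, alpha or decision rule, so that inference is not supported. What stands is narrower: the plan offers nothing but separate intervals to compare.
- **Confounding by severity is not shown.** Eligibility criteria are identical, both cohorts are consecutive, and prospective patients need an indication for arthroscopy before they are eligible. Recruitment {15} also involves all hand surgeons in screening, which could bring in milder tears. Silence about flagging in the historical cohort is not evidence of a difference. This is accepted: distortion by stage mix is a risk of unknown direction.
- **Stage may not be available for both cohorts.** A reader might assume that the EWAS/Geissler stage is already on file for everyone. Section {18a} commits to it for the study's surgical reports. For historical patients Table 3 mentions only inspection of surgical reports, and {14} says those data came from clinicians who had no trial-specific instructions. A stage analysis is therefore conditional.
- **Detail belongs in an analysis plan, and the Discussion admits the lack of randomisation.** The choice of interval method and any stratification could well sit in a document not shown here, and their absence is not the point. The point is that the section stating the methods for the primary outcomes fixes per-test estimates against a comparative objective, that {7} and {8} rank this objective differently, and that {14} and {20c} answer heterogeneity with sample size. Admitting the limitation changes none of these.

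**Conclusion.** The point holds in this limited form. The stated analysis does not estimate the quantity that the second primary objective names, and the rank of that objective differs between {7} and {8}. Under assumed counts (19/20 v 28/40), separate intervals overlap while the difference interval is +2.9 to +41.0 points. At 0.90 v 0.70 a reader relying on non-overlap would see a difference with probability 0.04 to 0.25, against 0.23 to 0.55 with a difference interval, for 30% to 70% instable tears. All of these figures rest on assumed prevalence and accuracy.

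Stage mix could by itself create a gap of about 5 to 10.5 points under the assumed mixes; neither its presence nor its direction is established. The documented non-comparability is the blinding difference in {17a}. Adjustment for stage would not remove it, because the historical stage itself was assigned by surgeons who knew the imaging result. With the low precision in step 3, this supports a descriptive label for the comparison. Since all analyses are declared exploratory, the plan should be corrected on this point, but the estimation of 4D CT accuracy itself is not undermined.

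**What to change.** 1. In {20a}, state the comparison estimate: the unpaired difference (4D CT minus cineradiography) in sensitivity, in specificity and in AUC, each with a 95% interval, for example Newcombe for the two proportions.
2. Report the stage distribution of each cohort, and sensitivity by stage (III v IV–V), as a descriptive sensitivity analysis where the historical surgical reports allow staging. State how many historical patients could be staged.
3. Reconcile {7} and {8} by labelling the comparison secondary and descriptive in both. Cite the blinding difference in {17a} as a reason, and do not present the larger historical cohort as a remedy for bias.

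The cost is wording, plus reading stage from historical reports where it is stated; no additional patients are needed. The stage-specific figures will be imprecise: if 20 instable 4D CT wrists split 12 and 8, a result of 7/8 has a Wilson interval of about 53% to 98%. A further stratifier would not be workable with numbers of this size.
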